### Ethical Considerations

This study was reviewed and approved by the local Ethics Committee of Hospital Israelita Albert Einstein (CEP Einstein), São Paulo, Brazil, registered under IRB00005041, in accordance with applicable national and international regulations (CAAE number 82494524.0.1001.0071). A waiver of written informed consent for patients was granted, as the study is strictly observational and involves no intervention in routine clinical care, no modification of clinical management, and no access to patients’ medical records. Only chest radiographs obtained as part of standard care were used, and all images were fully anonymized prior to storage and analysis, with no directly identifiable information included in the research dataset. However, written informed consent was obtained from the physicians responsible for enrolling patients in the LuAna trial, as they are considered direct research participants.

All data are handled under strict confidentiality procedures. Chest radiograph images were collected via the LuAna app and stored in an anonymized format on a secure cloud-based server.

The analytical database contains exclusively deidentified data. Access to identifiable information at the study sites, when applicable, is restricted to authorized local investigators. Study data will be securely stored at the hosting institution for a minimum of 5 years, in compliance with institutional and regulatory requirements.

Posttrial access pathways for the tool will be discussed with the Brazilian Ministry of Health to ensure continuity if the intervention proves beneficial. Technical details of the algorithm, including its development, training, validation, and performance characteristics, will be described in accordance with the CLAIM (Checklist for Artificial Intelligence in Medical Imaging) reporting guidelines [40], complementing the CONSORT-AI and SPIRIT-AI standards applied to the clinical trial components [32,33].

### Outcomes

#### Primary Outcome

The primary outcome is expected to show that AI support improves physicians’ ability to detect radiographic abnormalities, including consolidation or pulmonary opacity, pneumothorax, atelectasis, pleural effusion, and cardiomegaly. Physicians are anticipated to be more likely to correctly identify at least 1 of these 5 findings when assisted by AI than when interpreting CXRs unaided. This outcome is defined as a patient-level binary indicator of whether the physician correctly identifies any of the 5 prespecified findings compared with the thoracic radiologist’s reference standard.

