**Objective:**

This study aims to evaluate whether AI assistance enhances physicians’ ability to detect key radiographic abnormalities, including consolidation or pulmonary opacity, pneumothorax, atelectasis, pleural effusion, and cardiomegaly. The primary outcome is the difference in physicians’ diagnostic accuracy (per examination) when assisted by the AI tool compared with usual practice, using expert radiologist consensus as the reference value.

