**Figure 3. F3:**
[figure not shown]
Workflow for chest X-ray (CXR) interpretation in control and intervention groups. Top panel (control group—without AI): CXRs from patients with respiratory complaints are interpreted solely by the physician (1), without access to AI support (2). Bottom panel (intervention group—with AI): physicians first perform an initial assessment of the CXR (1) and register their findings via the LuAna mobile app (2). After this, the AI model processes the image and returns a score and a heatmap highlighting abnormal regions (3). The physician can then review and, if needed, revise their interpretation based on the AI output (4). Both pre- and post-AI interpretations are recorded for analysis. For both groups, CXR assessments are compared against a reference standard, defined as thoracic radiologist evaluation performed on the CARPL, with reports independently double-validated by thoracic radiologists blinded to both the physician assessment and AI output. The primary outcome is the comparison of radiologic findings detection rates before and after AI assistance relative to the reference standard. The workflow includes data acquisition at the study centers, followed by radiologist annotation, primary and secondary end point evaluation, and statistical analysis at the coordinating center. AI: artificial intelligence; CARPL: Clinical Artificial Intelligence Research Platform for Labeling.

Only demographic variables, including age group, sex, and race, will be collected in aggregated form to characterize the study population and allow for fairness analyses, ensuring equitable and unbiased AI performance. CXRs will be captured either by photographing printed films positioned on a lit negatoscope, by photographing digital images displayed on a picture archiving and communication system monitor, or by direct screen capture, all following strict protocols to guarantee full anonymization. Physicians will capture only the thoracic image, ensuring that all patient identifiers are systematically removed and never visible. A patient ID entered solely to return the radiologist’s report to the local health unit will be encrypted and remain inaccessible to the research team. Nondiagnostic images or studies failing predefined quality-control criteria will be excluded from analysis.

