### Reference Standard Generation, Report Return, and Critical Findings

The radiologists are responsible for producing the ground-truth (reference standard) for all CXR images during the study. The first step in ground-truth generation is to assign 2 thoracic radiologists to independently interpret the CXR images to set up the reference standard, classifying each finding as “normal” or “abnormal.” The correct classification matches the reference standard. For cases classified as *abnormal*, the presence or absence of the relevant radiological findings (consolidation, pulmonary opacity, pneumothorax, atelectasis, pleural effusion, and cardiomegaly) will be assessed, as well as the presence or absence of changes suggestive of TB. Based on these evaluations by the 2 thoracic radiologists, the ground truth is established. The radiologists will be blinded to both the physicians’ interpretations and the AI outputs.

A chest radiograph will be labeled as suggestive of pulmonary TB if at least 1 radiographic feature considered compatible with pulmonary TB is present, as determined by the adjudicated thoracic radiologist reference standard. Examples include cavitation, upper-lobe–predominant consolidation or opacities, fibronodular changes or scarring with upper lobe volume loss, or a miliary pattern. If none of these features is present, the examination will be labeled as “not suggestive of pulmonary TB.”

For physician performance analyses, an examination will be considered correctly classified when the physician’s binary classification (normal vs abnormal; suggestive vs not suggestive of pulmonary TB; presence or absence of specific radiographic patterns) matches the adjudicated thoracic radiologist reference standard. In cases of any disagreement between the 2 experts in any of the evaluated items, a third radiologist, more senior, will adjudicate.

All findings will be registered in the CARPL, with abnormalities annotated to allow direct comparison with AI outputs. This will serve as the reference value for model validation and performance analysis (Figure 4).

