### Statistical Analysis

The sample size was calculated to detect a minimum difference of 10% in the primary outcome—a binary indicator of whether the physician correctly labeled a CXR—between the AI-assisted and control groups. The calculation accounted for the stepped-wedge cluster-randomized design with batched implementation using the following assumptions: 9 clusters randomized in 3 batches to cross over from control to intervention, 10 time periods, a baseline detection rate of 67% in the control group, an expected increase to 77% in the intervention group, and an intracluster correlation coefficient ranging from 0.001 to 0.003.

The design effect was adjusted for the correlation structure induced by repeated measures within clusters over time using methods described by Hussey and Hughes [28] and extended to account for batched randomization, as described by Hemming et al [35,36]. The power calculation targeted 80% power at a 2-sided significance level of 5% and accounted for potential variability in cluster sizes. The final average cluster size was 37, and the overall sample size was inflated by 10% to account for anticipated exclusions due to image quality issues or missing data (dropout). This approach ensures adequate power to detect a meaningful effect of the intervention while maintaining the integrity of the stepped-wedge design with staggered implementation across batches.

Primary analysis will follow the modified intention-to-treat principle. All eligible CXRs (the unit of analysis in this study) will be analyzed according to the study group (control or intervention), to which their corresponding cluster was allocated at the time of image acquisition, regardless of physician adherence to the intervention or exposure to AI output. Images of poor quality, as defined by our radiologists, will be excluded postrandomization.

The primary outcome analysis will use a generalized linear mixed model with a binomial distribution and logit link function to estimate the effect of the AI-assisted intervention on detection probability. The model will include fixed effects for the intervention group (AI-assisted vs control), calendar time (to adjust for secular trends), time since intervention rollout (to account for learning or adaptation effects), and batch effects. In addition, random intercepts for clusters will be specified to account for intracluster correlation.

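### The primary outcome is stated in conflicting ways, and its one explicit definition neither penalises false findings nor says how to score a film with none of the five

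*Protocol article*

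**What the plan says.** The protocol article states the primary outcome in four places, in four forms.

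- **Abstract, Objective:** "The primary outcome is the difference in physicians’ diagnostic accuracy (per examination) when assisted by the AI tool compared with usual practice".
- **Figure 3 legend:** "The primary outcome is the comparison of radiologic findings detection rates before and after AI assistance relative to the reference standard".
- **Statistical Analysis, sample size:** "a binary indicator of whether the physician correctly labeled a CXR". The same section calls the 67% control value a detection rate and says that the mixed model estimates a detection probability.
- **Outcomes, Primary Outcome:** "a patient-level binary indicator of whether the physician correctly identifies any of the 5 prespecified findings", explained in the sentence before it: "Physicians are anticipated to be more likely to correctly identify at least 1 of these 5 findings when assisted by AI". This is the only place worded as a definition.

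Two further statements bear on scoring. The reference-standard section counts a physician's binary call as correct when, among other items, the "presence or absence of specific radiographic patterns) matches the adjudicated thoracic radiologist reference standard". The Statistical Analysis section takes all eligible radiographs as the analysis set, apart from those of poor quality. Because the reference standard includes a normal class, films with none of the five findings are expected.

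**The concern.** Accuracy counts true negatives and false positives. A detection rate does not. They are different estimands, with different denominators unless every film carries a finding.

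Read literally, the explicit definition is one-sided. One true hit is full success, whatever else was called and whatever else was missed. A reader who marked all five findings on every film would score 100% on every film that carries a finding. For films that carry none, no value is stated.

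At stake is what a positive result would mean. The abstract speaks of improved accuracy, but the defined endpoint could improve because physicians call more findings after seeing AI output, with accuracy unchanged or worse. An open choice among four forms also allows the favourable one to be picked after the data are seen.

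**Working it through.** **1. The forms side by side**

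| Place | Quantity | False finding counts against? | Film with none of the five |
|---|---|---|---|
| Abstract, Objective | Accuracy per examination | Yes | Scored |
| Figure 3 legend | Detection rate | No | Not stated |
| Sample size | Film correctly labelled; also called a detection rate | Unclear | Unclear |
| Primary Outcome | Any, or at least 1, of five correctly identified | No | Not stated |
| Reference-standard section | Match on presence or absence, per item | Yes, per item | Scored per item |

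The last row would settle false positives, but the Primary Outcome section does not invoke it and nothing says how five matches become one indicator. Joined to the word any, one correct absence call would be enough. Success would then be almost automatic, which is hard to square with a 67% baseline. Only an all-findings match or a normal/abnormal match would penalise over-calling.

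**2. The planned effect from a threshold shift alone**

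Inputs: 0.67 and 0.77 (Statistical Analysis), taken here as hit rates on films with a finding. Assumption: an equal-variance binormal reader with fixed AUC. Then d = √2·Φ⁻¹(AUC), the threshold is t = d − Φ⁻¹(sensitivity), and specificity = Φ(t).

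For AUC 0.80, d = 1.190.
- Sensitivity 0.67: t = 1.190 − 0.440 = 0.750, specificity 0.77.
- Sensitivity 0.77: t = 1.190 − 0.739 = 0.451, specificity 0.67.

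The same steps give 0.70 to 0.59 at AUC 0.75, and 0.85 to 0.77 at AUC 0.85.

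Now count a film with a finding as correct if hit, and a film without as correct if nothing is called. With prevalence π, the change in accuracy is π(0.10) − (1 − π)(0.10) at AUC 0.80.
- π = 0.30: 3 − 7 = −4 points
- π = 0.50: 5 − 5 = 0
- π = 0.70: 7 − 3 = +4 points

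The endpoint as worded would show +10 points in all three cases.

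**3. Films with none of the five**

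*Coded 0.* The success rate cannot exceed π, so 77% requires at least 77% of films to carry a finding.

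*Dropped.* The plan's own figure is an average cluster size of 37 for 80% power. I could not confirm it: the article does not say whether 37 is per city or per city-period, and the schedule figure is not shown. The check uses the Hussey-Hughes variance with 9 clusters, 3 batches of 3 clusters, 4 periods per batch, binomial variance averaged over the two arms, and ICC 0.003 to 0.001. With 37 per city-period, power is 0.73 to 0.76 with batch-specific period effects, and 0.93 to 0.94 with common period effects and batches starting at periods 1, 4 and 7. With 37 per city in total (N = 9 × 37 = 333), power is only 0.16 to 0.44 across the layouts tried. Keeping only films with a finding multiplies the cell size by π:

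| π (assumed) | Films per cell | Power, batch-specific periods | Power, common periods |
|---|---|---|---|
| 1.0 | 37 | 0.73–0.76 | 0.93–0.94 |
| 0.7 | 25.9 | 0.59–0.61 | 0.83–0.85 |
| 0.5 | 18.5 | 0.46–0.48 | 0.70–0.72 |
| 0.3 | 11.1 | 0.31–0.32 | 0.50 |

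**4. Why the risk is not idle here**

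The tool's per-finding specificity is 0.49 to 0.85 in Table 1 and 0.70 to 0.92 in Table 2, so false flags will be common. These values illustrate the risk and do not measure it (see the objection).

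**The case against.** The best reply is that the reference-standard section already has a match rule, that it agrees with accuracy per examination and with a correctly labelled film, and that a condensed article may leave the combining rule to a fuller document. Part of this stands: the article as a whole does not exclude counting false positives, and a missing combining rule would by itself be no finding. It does not remove the conflict, because the only explicit definition states a different rule.

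Other replies limit the claim. Four stronger readings are tempting, and the documents do not support them.

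- *That the endpoint cannot be scored on a film without a finding.* It could be coded 0. The exact statement is that no rule is given.
- *That the 67% and the power calculation belong to another endpoint.* The same section ties the 67% to correct labelling and also calls it a detection rate. Its denominator is not shown either way.
- *That Tables 1 and 2 give the share of clean films falsely flagged.* Each specificity is measured on films lacking that one finding, which may show others. The tables list six classes, while the endpoint merges consolidation and opacity to make five.
- *That physicians will accept the false flags.* They read unaided first and revise only if they see need, and training presents the output as advisory. No uptake figure exists.

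Secondary analyses offer partial protection. Separate models per finding are planned, and the secondary outcomes text expects better specificity and predictive values. But Textbox 1 ties those metrics to the AI outputs, and none of them qualifies the primary test.

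**Conclusion.** The concern holds as a defect of definition and must be fixed before analysis. The primary outcome has incompatible forms, and the only explicit one can show the full planned benefit from over-calling alone.

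The size is conditional. At a reader AUC of 0.80, a rise from 67% to 77% can coexist with a specificity loss of about 10 points and an accuracy change between −4 and +4 points over prevalences of 30% to 70%. Reader AUC, the binormal form and the prevalence are assumptions. The power loss from dropping finding-free films depends further on the unstated layout and on the unit of the 37. None of this shows that over-calling will occur, only that the endpoint as worded could not tell it from a gain in accuracy.

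**What to change.** Amend by a dated change made without sight of outcome data by phase.

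1. Use one primary definition in the Abstract, the Figure 3 legend, the reference-standard section, Statistical Analysis and Primary Outcome, scored on every eligible film.
2. Count a film with none of the five reference findings as correct only if none of the five is called.
3. State the combining rule for films with a finding. The at-least-one rule still leaves extra false findings unpenalised on these films. If it is kept, report physician sensitivity and specificity per finding and by phase, with 95% CIs, beside the primary result. Do not describe a gain as improved accuracy if physician specificity falls.
4. State which definition and denominator the 67% and 77% refer to, and restate the power if they do not match the chosen one.

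No new data are needed, since physicians and radiologists already record presence or absence of the findings. The costs are a mid-trial amendment, as collection began in January 2026, and possibly a smaller observed effect or lower stated power.

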#### Secondary Outcomes

The secondary outcomes are expected to demonstrate that AI assistance increases detection rates for each of the 5 radiographic findings, as well as overall pulmonary abnormality and TB-related patterns, relative to unaided physician interpretation. Improvements in abnormality localization accuracy are also anticipated, both for the AI outputs alone and for physician interpretations after reviewing AI results. Diagnostic performance compared with the reference standard is expected to improve, with higher sensitivity, specificity, AUC, positive predictive value, and negative predictive value, reflecting greater reliability in identifying clinically relevant radiological abnormalities. The secondary outcomes are depicted in Textbox 1.

Textbox 1.Secondary objectives and outcomes.Secondary objectivesMeasure the effect of artificial intelligence (AI) on physicians’ detection rates for each of the 5 radiologic findings independently, pulmonary abnormality, and features suggestive of pulmonary tuberculosisEvaluate AI algorithm performance in a real-world settingEvaluate physicians’ experiences regarding usability of the mobile interfaceAssess the impact of external influencing factors on AI algorithm predictionsEvaluate physicians’ learning related to interpretation of radiologic findings on chest X-rays (CXRs) before and after the interventionSecondary outcomesWhether the physician correctly identifies each of the 5 radiologic findings, pulmonary abnormality, and features suggestive of pulmonary tuberculosis on chest radiographsComparison between AI algorithm outputs for CXRs and thoracic radiologist reference standard classifications to calculate sensitivity, specificity, area under the receiver operating characteristic curve, positive predictive value, and negative predictive valueResponses to questions regarding the mobile app interface, responsiveness, and functionality measured using a 7-point Likert scaleAssociations between AI algorithm outputs for CXRs and CXR characteristics, including photo quality, presence of thoracic devices, and technical artifacts, as labeled by radiologistsChange in physician interpretation performance over time and according to the duration of participation in the study

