### Study Design: Stepped-Wedge Randomized Design

The stepped-wedge cluster-randomized design was chosen for this trial because of its clear methodological benefits. Unlike parallel designs, all clusters eventually receive intervention, enhancing acceptability in clinical settings where prior evidence suggests potential benefit [28,29]. The phased implementation also mirrors real-world logistical constraints while allowing for both within- and between-cluster comparisons, thereby improving statistical efficiency and power [28,30]. Additionally, repeated measurements over time enable adjustment for secular trends, strengthening causal inference [28-31]. These characteristics make the stepped-wedge design especially suitable for pragmatic evaluations of health care interventions.

This nationwide, multicenter, stepped-wedge cluster-randomized trial (SW-CRT) follows the CONSORT-AI (Consolidated Standards of Reporting Trials-Artificial Intelligence) and SPIRIT-AI (Standard Protocol Items: Recommendations for Interventional Trials-Artificial Intelligence) guidelines [32,33]. It will evaluate whether AI can improve CXR interpretation in routine clinical care across Brazil. Cities will act as clusters, comprising public, private, and philanthropic health care units to ensure broad socioeconomic and geographic representation [28,30,31,34]. All clusters will begin in the control condition (standard physician interpretation) and will cross over to the intervention (AI-assisted physician interpretation) at randomly assigned monthly intervals. Potential contamination across clusters will be minimized by selecting independent clinical units with nonoverlapping staff and workflows.

A batched stepped-wedge approach allows staggered initiation, accommodating operational constraints while minimizing contamination or learning effects. Once a cluster transitions, it remains in the intervention arm (Figure 2). Simple urn-based randomization without replacement will occur independently in each batch. Participating centers within cities must have infrastructure for CXR interpretation (negatoscope or digital screen), reliable internet access, and commitment to study protocols.

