## Discussion

### Principal Findings

This trial is a pivotal effort to evaluate how AI can enhance diagnostic accuracy, clinical workflows, and physician performance in interpreting chest radiographs.

By using a batched stepped-wedge cluster-randomized design across a nationally representative sample of health care settings, we aim to rigorously assess the real-world utility of LuAna, an AI-powered platform for CXR interpretation developed in the public sector to assist general practitioners.

Despite ongoing debate about the advantages of SW-CRTs, including concerns about equipoise and delayed access to interventions [41], this design offers distinct benefits for implementation research. Governed by the same ethical principles as all clinical research [42], SW-CRTs are particularly valuable when evaluating innovations that are expected to be beneficial and for which withholding access may be contentious [42]. In the SUS context, this approach ensures that all centers ultimately gain access to AI support, promotes fairness and acceptability, and provides a pragmatic pathway to sustainable integration of the intervention into routine care.

The central goal is to determine whether LuAna improves clinicians’ ability to detect radiographic abnormalities, particularly in environments with limited access to radiology expertise. Comparisons against adjudicated, double-blinded radiologist interpretations will enable the quantification of diagnostic agreement, while stratified analyses by site type and physician characteristics will offer insights into contextual factors that may influence AI performance.

Importantly, the trial also investigates the clinical impact beyond diagnostic accuracy. By evaluating patient management decisions and turnaround times, we aim to capture how AI affects treatment pathways and efficiency in routine care. Usability assessments will provide critical feedback for refining and scaling the platform, thereby ensuring seamless integration into diverse clinical workflows across both mobile and desktop interfaces.

Robustness will be evaluated through sensitivity analyses on image quality, artifacts, and medical devices, thereby validating the model’s generalizability under real-world conditions. Additionally, longitudinal analysis of physician interpretations will explore whether repeated AI exposure improves independent performance, highlighting AI’s potential educational role.

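### The physician-learning outcome is defined as a trend over time and duration of participation, which under one-way crossover cannot separate learning from AI exposure from calendar change

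*Protocol article*

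**What the plan says.** The last secondary objective in Textbox 1 (Secondary Outcomes) is physicians' learning before versus after the intervention. The matching outcome is change in "physician interpretation performance over time and according to the duration of participation in the study". It names no comparison between AI-exposed and unexposed cities, and it does not say whether the first or the final reading is scored.

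Principal Findings in the Discussion states the aim in causal terms: "longitudinal analysis of physician interpretations will explore whether repeated AI exposure improves independent performance".

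The design section says that clusters "will cross over to the intervention (AI-assisted physician interpretation) at randomly assigned monthly intervals", and "Once a cluster transitions, it remains in the intervention arm".

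In intervention periods the physician registers a reading before any AI output is shown (Data Collection and Figure 3). The Figure 3 caption adds: "Both pre- and post-AI interpretations are recorded for analysis".

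The Statistical Analysis section gives the primary model fixed effects for intervention, "calendar time (to adjust for secular trends), time since intervention rollout (to account for learning or adaptation effects), and batch effects". It then extends separate models to each finding, pulmonary abnormality and TB. Learning is not on that list.

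**The concern.** The objective asks what AI exposure does to a physician's own reading. The outcome as worded measures how performance moves with time. Within a city, AI exposure always comes after the control months. A rising trend could therefore reflect AI learning, a change in case mix or season, or growing familiarity with the structured form.

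The article itself treats secular trend as a threat and adjusts the primary analysis for it. If the learning outcome is followed as written, the educational conclusion would rest on an uncontrolled before-after comparison. Yet the same trial holds concurrent controls for this question: unaided readings from cities that have not crossed over, made in the same month as pre-AI readings from cities that have.

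**Working it through.** The article gives no figure for the learning outcome, so there is none to reproduce.

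**Inputs from the article (Statistical Analysis, Study Design):** 9 clusters in 3 batches, 10 periods, one-way crossover at monthly steps, 67% versus 77%, ICC 0.001 to 0.003, average cluster size 37.

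**Assumptions:** the rollout layout (Figure 2 is not shown, so several layouts were tried), a drift of 0.5 to 1 point per month unrelated to AI, and 37 read as films per city-month. The article does not say which unit 37 refers to. Under that reading, power for the primary outcome is 91-97% in five layouts with common period effects and 72-75% in a sixth. If 37 is the total per city, power is 22-28%. The stated 80% target therefore does not settle the unit.

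**1. Duration cannot be separated from calendar time.** For a city that starts in period s, duration in period t is d = t − s + 1. Given city effects (which absorb s) and calendar-period effects (which absorb t), d adds no information. The rank added was 0 in all six layouts. With no learning and a drift of 1 point per period, the duration slope is therefore 1.0 point per period, all of it drift.

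**2. Size of a before-after difference with no learning.** Take a city followed for T periods that crosses over after period k.
- Mean intervention period = (k + 1 + T)/2; mean control period = (1 + k)/2.
- Difference = T/2, whatever k is.
- T = 4 (short batches): 2.0 periods. T = 10 (followed throughout): 5.0 periods.
- At 1 point per period: 2.0 to 5.0 points. At 0.5 point: 1.0 to 2.5 points.

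Pooling city-months instead of working within cities gives the same order. With one of nine cities crossing each month, the mean control period is 165/45 = 3.67 and the mean intervention period is 330/45 = 7.33, a gap of 3.67 months. Over five layouts the gap was 2.67 to 3.83 months. That gives 0.5 × 2.67 = 1.3 points up to 1.0 × 3.83 = 3.8 points.

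**3. The concurrent contrast on first readings.** Control readings are unaided, and so is the first reading in intervention periods. Comparing crossed with uncrossed cities in the same period cancels a drift that all cities share. With calendar-period adjustment, the bias was 0 under the same linear drift in all six layouts, and a true gain of 5 points was recovered as 5.0.

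**4. Precision of that contrast.** For a constant effect, the gain detectable with 80% power was 7.3 to 11.0 points.
- SE = 7.3/2.80 = 2.6 to 11.0/2.80 = 3.9 points, where 2.80 = 1.96 + 0.84.
- Power for 5 points, Φ(5/SE − 1.96): 48% down to 25%.
- Power for 3 points, Φ(3/SE − 1.96): 21% down to 12%.

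Letting the effect vary with months since rollout cannot make the averaged contrast more precise, so these figures are upper limits for that analysis.

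**The case against.** The strongest reply is that Textbox 1 lists an outcome and does not give an analysis. No model for learning is stated, the article is condensed, and a SAP may adjust for calendar time. The authors plainly know the issue, because the primary model carries both calendar time and time since rollout. This has weight. The confounding comes from how the outcome is worded and is not inherent in the stepped-wedge design; the primary model's form, applied to first readings, would deal with it. What remains is more than missing detail: the outcome as fixed answers a different question from the objective beside it, and the calendar-adjusted models are assigned to other outcomes by name.

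Two stronger readings are tempting and not supported.
- A reader might infer that AI-assisted final readings will be scored, so that the whole planned gain of 77 − 67 = 10 points would appear as learning. Textbox 1 does not exclude this, but the Discussion's reference to independent performance points to unaided reading.
- A reader might infer that the pre-AI readings go unused. They do not: the Figure 3 caption says "The primary outcome is the comparison of radiologic findings detection rates before and after AI assistance relative to the reference standard". Only the concurrent randomised contrast for learning is unstated.

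It is also fair to say that physicians who join at different dates would partly separate duration from calendar time. That variation is not randomised, however.

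**Conclusion.** The point holds for this secondary outcome and leaves the primary result untouched. Followed as worded, the outcome cannot attribute a change in reading performance to AI exposure. Under the assumed drift and layouts, about 1 to 5 points of apparent learning could arise with no true learning. The article documents no drift, so this range illustrates sensitivity and does not estimate a bias that will occur. The identification problem itself does not depend on the layouts: it follows from one-way crossover and the definition of duration. The scored reading also needs to be named, though the Discussion already indicates which one is meant.

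**What to change.** State that the learning outcome is scored on unaided first readings only: control-period readings, and the pre-AI reading in intervention periods. Analyse it with the form of the primary model, adjusted for calendar period and batch, with cluster random intercepts.

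Report as the learning effect the contrast between AI-exposed and not-yet-exposed cities, either as a function of months since rollout or averaged over them. The rollout coefficient alone should not be used. With months since rollout in the model, it is only the step at rollout, when exposure is least, and accumulated learning sits largely in the other term. Keep the trend by duration of participation as description.

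The cost is a change of wording, best made before the data are examined; nothing new has to be collected. Two downsides should be stated with it:
- The interval will be wider than that of a pooled time trend, and power for small gains is low, as shown above. That argues for reporting the interval plainly, not for relying on the trend.
- First readings made in the knowledge that AI output will follow may differ in effort. The contrast therefore measures unaided reading when AI is available, which may mask or mimic learning.
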